**Figure 2. F2:**
[figure not shown]
Light needle therapy between LU7 and LU9.

### 2.6. Outcome measurements

Outcome measurements will consist of subjective reporting of heroin use, quality of life, and objective urinary morphine levels. The primary outcomes are urinary morphine levels and self-reported times or days of heroin use during the previous week before and after the 4-week intervention period. The secondary outcomes are self-reported visual analogue scale (VAS) scores (0–10) for heroin craving/refusal to use heroin in the previous week and quality of life using the Short Form-12v2® (SF-12v2) before and after a 4-week intervention. The participant’s pulse diagnosis and heart rate variability before and after 4 weeks of intervention will be documented.

A VAS score of 0 for heroin craving indicates no heroin craving, while a score of 10 indicates the strongest craving. A VAS score of 0 for refusal to use heroin means no refusal, whereas a score of 10 indicates complete refusal. The SF-12v2 Health Survey is a multipurpose, short-form health tool consisting of 12 questions that generates an 8-domain overview of functional health and well-being (Physical Functioning, Role-Physical, Bodily Pain, General Health, Vitality, Social Functioning, Role-Emotional, Mental Health), 2 psychometric-based summative measures of physical and mental health, and a preference-based health utility index. PRO CoRE is part of the Smart Measurement® System product suite and QualityMetric’s upgrade to QualityMetric Health Outcomes™ scoring software, which will be used to score the SF-12v2 Health Survey.

Reasons for participants not completing follow-up or withdrawing from the study include adverse events/comorbidities, poor response to treatment, failure to return to follow-up, failure to meet selection criteria at enrollment, other breaches of the protocol, and denial of treatment. These will be documented as potential adverse events.

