### 2.4. Sample size and randomization

We calculated a sample size of 98 in accordance with a 2-way repeated-measures analysis of variance with a medium effect size of 0.25, pre- and post-measurements for each of the 2 groups, a significance level (*α*) of 0.05, and a desired power (1–*β*) of 0.80.^[28]^ Expecting a 2% dropout rate, 100 participants will be recruited. A random permutation block of block size 4 is selected using a research randomizer that generated a random sequence.^[29]^ Allocation concealment was performed by using numbered containers. The researchers recruited and assessed participants in sequentially numbered, opaque, sealed, and stapled envelopes. Trial participants, outcome assessors, and data analysts will be blinded after assignment to interventions labeled A and B for both groups.

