### 2.7. Statistical analysis

Data will be displayed as mean ± standard deviation. Baseline participant characteristics between the experimental and control groups will be assessed and compared using independent *t* tests and chi-square tests. The differences between the 2 groups will be compared using an independent *t* test. Paired *t* test will be used to compare the 2 groups. All analyses will be performed using the Statistical Package for the Social Sciences (SPSS) for Windows version 22 (Statistics 22, IBM Corp., Armonk, NY). Statistical significance is set at P < .05.

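### Two unranked primary outcomes share one flat 0.05 threshold with no success rule: if either one suffices, the family-wise error exceeds 5% (up to 9.75% for two tests); if both are needed, joint power is below the per-outcome power.

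*Protocol article*

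**What the plan says.** Section 2.6 of the protocol article defines the primary endpoint in the plural: "The primary outcomes are urinary morphine levels and self-reported times or days of heroin use during the previous week". Both are measured at baseline and again once the 4 weeks of treatment are over. It does not rank urinary morphine against self-report. For self-report it does not choose between times and days; the abstract leaves the same choice open, using episodes in place of times. Section 2.6 itself describes the urine measure as objective and the heroin-use report as subjective.

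Section 2.7 gives one general rule: "Statistical significance is set at P < .05". It states no order of testing, no division of alpha and no condition for calling the trial positive.

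Section 2.4 sizes the trial with a "2-way repeated-measures analysis of variance with a medium effect size of 0.25". The other inputs are two arms measured twice, 80% power and, for alpha, "a significance level (*α*) of 0.05". The result is 98, raised to 100 for 2% dropout. The calculation does not name the outcome it is for, nor the effect in the analysis of variance that it targets.

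**The concern.** With two primary outcomes, what counts as a positive trial depends on a rule that the article does not give.

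- **Either outcome suffices.** Two chances at 0.05 make the overall false-positive rate higher than 0.05.
- **Both are required.** The error rate is controlled, but the chance of success is lower than the power for each outcome.

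The choice has weight here because the two outcomes differ in kind. As written, a significant self-report result alongside a null urine result could be presented as a positive trial, and a reader could not tell whether that had been planned. The open choice between times and days adds a possible third test.

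**Working it through.** **Inputs.** From the article: at least two primary outcomes (2.6); threshold 0.05 (2.7); sample size 98, alpha 0.05, power 0.80, effect size f = 0.25, two groups, two measurements, 2% dropout (2.4). Assumed, because not stated: two-sided tests; the correlation between the test statistics for the two primaries (range shown); a pre-post correlation of 0.5 within an outcome.

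**1. The plan's own figure.** For the between-groups effect in a repeated-measures analysis of variance with m = 2 measurements and pre-post correlation ρ, the noncentrality is λ = N·f²·m / [1 + (m − 1)ρ]. With N = 98, f = 0.25 and ρ = 0.5, λ = 98 × 0.0625 × 2 / 1.5 = 8.17. On 1 and 96 degrees of freedom at 0.05 this gives power 80.8%. N = 96 gives 79.9%, so 98 is the smallest even total that reaches 80%. Dropout: 98 / 0.98 = 100. Both stated numbers reproduce, with one test at the full 0.05.

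**2. Either outcome suffices, two tests.** If independent: 1 − 0.95² = 0.0975. For correlated tests, the rate is one minus the bivariate normal probability that both statistics lie within ±1.96:

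| Correlation | At least one false positive |
|---|---|
| 0 | 9.75% |
| 0.3 | 9.5% |
| 0.5 | 9.1% |
| 0.8 | 7.8% |
| 0.9 | 7.0% |

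The rate approaches 5% only as the correlation approaches 1.

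**3. Times and days tested separately, three tests.** If independent: 1 − 0.95³ = 0.1426. By simulation: about 12.5% if all correlations are 0.5, and about 10.8% if times and days correlate 0.9 and each correlates 0.5 with urine.

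**4. Both must be significant.** The false-positive rate is at most 5%. If each outcome has exactly 80% power, joint power is 0.80² = 64% if independent, 68.7% at correlation 0.5, 72.9% at 0.8 and 75.0% at 0.9.

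**5. What an alpha adjustment costs.** Holm tests the smaller of the two P values at 0.025 first. At N = 98 and λ = 8.17, power at 0.025 is 71.9%, against 80.8% at 0.05. Under the same assumptions, keeping 80% at 0.025 would take 118 analysed participants.

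**6. Dependence on the effect that was sized.** For the group-by-time interaction, λ = N·f²·m / (1 − ρ) = 98 × 0.0625 × 2 / 0.5 = 24.5. Power is then 99.8% at 0.05 and 99.6% at 0.025. With that effect, the same inputs would need only 34 participants to reach 80%, which is not the stated 98.

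**The case against.** The strongest reply is that this is a condensed article, and multiplicity procedures are commonly left to an analysis plan that is not shown. The threshold in section 2.7 is generic and would be compatible with adjusted P values. This stands in part: the article does not prove that each primary will be tested unadjusted. But choosing the primary outcomes and the alpha used for sizing are decisions that the article does make. It makes them as several unranked outcomes and one calculation at the full 0.05. A later alpha split or a both-required rule would have consequences for power that section 2.4 does not reflect.

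Two stronger readings are tempting and should not be drawn.

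- A reader might infer that the false-positive rate simply is 9% to 10%. The documents do not support this. It requires that either outcome suffices, on which the article is silent, and a correlation no higher than about 0.5. Both outcomes concern recent heroin use, so a higher correlation and a lower rate are plausible; a third test would push the rate above that range.
- A reader might infer that the sample size is inadequate under every success rule. That is not established. Section 2.4 does not say which effect was sized, and if f = 0.25 described the interaction, 98 participants would have ample power even at 0.025. The 64% joint power is likewise only the independence value.

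It is also fair to say that putting urinary morphine first is a preference. Other rules would close the gap equally well.

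**Conclusion.** The point holds in conditional form. The article names two unranked primary outcomes with one flat threshold and no success rule.

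- **If either suffices:** the family-wise error is above 5%, with a ceiling of 9.75% for two independent or positively correlated tests, and up to about 14% if times and days are tested separately.
- **If both are required:** the error is at most 5%, and the cost moves to power, which is 64% to 75% for correlations from 0 to 0.9 if each outcome has exactly 80%.

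These figures assume two-sided tests and correlations that the documents do not give. The power figures at 0.025 rest further on the between-groups effect with a pre-post correlation of 0.5. Because the missing rule decides what counts as a positive trial, it should be settled before unblinding.

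**What to change.** By dated amendment, with a matching registry update, before unblinding:

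1. In section 2.6, choose one self-report measure, times or days of use.
2. In section 2.7, state one of the following:
   - a fixed order at 0.05, for example urinary morphine (the objective measure) first, and self-report only if the first is significant;
   - Holm across the two primaries;
   - a requirement that both are significant, with the power restated in section 2.4.

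**Cost.** More than a wording change, since the trial is registered (2.1) and under way (2.2), but no extra enrolment is proposed. Under the fixed order, the first test keeps the full 0.05, and self-report cannot be claimed alone. Under Holm, the first test is at 0.025; power at that step falls from about 81% to 72% at 98 participants if the sizing was for the between-groups effect with pre-post correlation 0.5, so the stated power should be revised. Requiring both gives joint power below the per-outcome figure.

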### 2.7. Statistical analysis

Data will be displayed as mean ± standard deviation. Baseline participant characteristics between the experimental and control groups will be assessed and compared using independent *t* tests and chi-square tests. The differences between the 2 groups will be compared using an independent *t* test. Paired *t* test will be used to compare the 2 groups. All analyses will be performed using the Statistical Package for the Social Sciences (SPSS) for Windows version 22 (Statistics 22, IBM Corp., Armonk, NY). Statistical significance is set at P < .05.

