## Abstract

**Methods::**

We will enroll 100 participants with opioid use disorders receiving methadone maintenance treatment at an addiction treatment center and randomly allocate them to an experimental or control group. The experimental group will receive 12 sessions of light needle therapy within 4 weeks, while the control group will receive sham light needle treatment without any laser output. Urinary morphine levels were assessed before and after treatment. Participants will be asked to self-report their number of episodes or days of heroin use and heroin craving/refusal to use heroin in the previous week before and after treatment on a visual analogue scale score of 0 to 10. Quality of life will be reported using the Short Form-12v2 before and after 4 weeks of treatment. Pulse diagnosis and heart rate variability will be evaluated before and after treatment. Baseline patient characteristics will be compared between the groups using the independent *t* test and the *χ*^2^ test. Data between the 2 groups will be compared using generalized estimation equations, and paired *t* tests.

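### Urinary morphine is to be shown as mean ± SD and compared by an unadjusted t test; if levels are markedly skewed and the effect is proportional, this costs much power

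*Protocol article*

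**What the plan says.** Section 2.7 of the protocol article gives a single summary and a single between-group test, with no exception by outcome: "Data will be displayed as mean ± standard deviation" and "The differences between the 2 groups will be compared using an independent *t* test". It adds "Paired *t* test will be used to compare the 2 groups". It names no transformation, rank test, count model, baseline covariate or handling of values at a detection limit.

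Section 2.6 puts two outcomes of concern here under that rule: "The primary outcomes are urinary morphine levels and self-reported times or days of heroin use during the previous week".

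The abstract names another analysis: "Data between the 2 groups will be compared using generalized estimation equations, and paired *t* tests". It states no link or distribution.

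Section 2.4 sizes the trial on a normal-theory model: "We calculated a sample size of 98 in accordance with a 2-way repeated-measures analysis of variance with a medium effect size of 0.25", at 80% power and with a 2% allowance for dropout.

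Section 2.3 admits adults with opioid use disorder who have been on methadone for at least a month. It requires neither current heroin use nor a positive urine test.

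**The concern.** A urine concentration is bounded below by zero and, in practice, by the assay's detection limit. Section 2.3 lets people with little or no recent heroin use enter alongside heavy users, so a pile-up of low values and a long right tail are to be expected. A few very high concentrations then dominate the arm means and inflate the SD. A real proportional fall in morphine can be missed for that reason alone. The sample size leaves nothing in hand to absorb the loss.

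Mean ± SD also describes such data poorly. For a lognormal variable the SD exceeds the mean once the log-SD passes √(ln 2) = 0.83, and mean minus one SD is then negative.

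The baseline value is collected in every participant but is not used as a covariate in the independent t test.

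**Working it through.** **The plan's own figure.** From section 2.4: f = 0.25, 2 groups, m = 2 measurements, α = 0.05, power 0.80. The correlation is not stated; take ρ = 0.5. For the between-group effect, λ = N f² m / (1 + (m − 1)ρ) = 98 × 0.0625 × 2 / 1.5 = 8.17. With F on 1 and 96 df this gives power 0.808. Then 98 / 0.98 = 100. The figure reproduces, with about one percentage point to spare, under normality.

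**Assumptions for morphine.** The documents give no SD, distribution, share of zeros or detection limit. Take 50 per arm (section 2.2), lognormal levels, a true shift of 0.5 SD on the log scale, a log-scale pre-post correlation of 0.5, and a two-sided 5% level. The shift is a ratio of exp(−0.5 × log-SD), that is 0.78, 0.61, 0.47 and 0.37 at log-SD 0.5, 1, 1.5 and 2.

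**Closed-form benchmarks on the log scale.**
- t test: noncentrality 0.5 × √(50/2) = 2.5 on 98 df, power 0.70.
- ANCOVA on baseline: the effect becomes 0.5 / √(1 − 0.5²) = 0.577, noncentrality 0.577 × 5 = 2.89 on 97 df, power 0.82.

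**Simulated power, 20,000 trials per column.**

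| Analysis | log-SD 0.5 | 1.0 | 1.5 | 2.0 |
|---|---|---|---|---|
| Raw post-treatment t | 65% | 52% | 36% | 24% |
| Raw change-score t | 56% | 35% | 20% | 12% |
| Raw ANCOVA on baseline | 75% | 59% | 39% | 26% |
| Log post-treatment t | 70% | 70% | 70% | 70% |
| Log ANCOVA on baseline | 81% | 82% | 81% | 81% |
| Rank ANCOVA on baseline | 78% | 79% | 78% | 78% |

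A smaller run of 3,000 trials gave 64%, 49%, 36% and 23% for the first row, so about 65%, 50%, 35% and 23% is a fair statement. With no effect, the raw post-treatment t test rejects in 5.1%, 4.1%, 3.4% and 2.5% of trials. Type I error is not inflated.

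The table separates two gains. At log-SD 0.5, baseline adjustment adds more (65% to 75% on the raw scale) than the log scale does (65% to 70%). From log-SD 1 upward the scale matters more.

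**Many values at the floor.** The ordering now depends on what the treatment changes.
- 40% of each arm at half the detection limit, users' control median at 20 times the limit, a shift of 0.8 log-SD among users only, 50 per arm: raw t against log t is 44% against 10% (log-SD 0.5), 56% against 26% (1.0) and 43% against 44% (1.5).
- 30% at the floor in both arms, shift among positives only, log-SD 1, 49 per arm: raw t 66%, log t 56%, Mann-Whitney 48%.
- 30% against 55% at the floor, no shift among positives, log-SD 1.5, 49 per arm: raw t 13%, log t 58%, Mann-Whitney 61%.

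**Weekly use, 49 per arm, assumed count and 0–7 day distributions.** There is no consistent direction. When mean use falls, raw t, log(1 + x) t and Mann-Whitney give for example 82%, 75% and 72% for counts, and 58%, 59% and 57% for days. When the effect is more people with zero use, they give 25%, 40% and 45% for counts, and 51%, 63% and 63% for days.

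**The case against.** The strongest reply has four parts.

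First, the article fixes no scale. A transformation could sit in an analysis plan that is not shown, and the abstract's generalized estimation equations could carry a non-normal family or link. This stands in part: analysis on the raw scale is what the text says when read plainly, not an explicit exclusion of transformation. But section 2.7 does name the summary and the test for all data, and any plan that departed from it would need to say so. The abstract shows that the analysis is unsettled; it does not supply a scale.

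Second, a reader might infer that both primary outcomes lose much power. The documents and the calculations do not support that. Days of use cannot exceed 7, so extreme values cannot arise there, and the t test is sometimes the better choice for weekly use.

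Third, a reader might infer that logging morphine always helps. It does not. With many values at the floor and an effect confined to users, setting floor values to half the limit and taking logs can do much worse than the raw t test.

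Fourth, the 80% for log-scale ANCOVA mixes two changes, and every power figure rests on an assumed log-SD. Both are true, which is why the table separates the two gains and shows a range. At log-SD 0.5 the scale alone is worth only about 5 points.

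Nor is the t test invalid here: its false-positive rate stays at or below about 5%.

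**Conclusion.** The point holds for urinary morphine, as a conditional loss of efficiency and a poor summary measure. If levels are roughly lognormal and the effect is proportional, the planned unadjusted comparison has about 65% power at log-SD 0.5 and about 23% at log-SD 2. A log-scale, baseline-adjusted analysis of the same participants has about 80%. The loss is modest with mild skew and large from a log-SD of about 1.

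The size rests on assumptions the article cannot confirm: the lognormal shape, the 0.5 log-SD shift and the correlation of 0.5. Baseline adjustment raised power over the unadjusted post-treatment test on the same scale in every lognormal setting shown. The advantage of the log or rank scale is conditional and can reverse when many values are at the floor. No general loss is established for weekly heroin use. The change is worth making because a primary outcome is affected, although the validity of the test is not in question.

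**What to change.** In section 2.7, and in agreement with the abstract, state one between-group analysis for each primary outcome.

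- **Urinary morphine:** compare post-treatment values between groups with the baseline value as covariate. Use the log scale if few values are at the detection limit, and report a ratio of geometric means with a 95% CI. Otherwise use a rank-based, baseline-adjusted analysis. State how values at the limit are handled, set the threshold for few in advance, and make the choice on blinded data before unblinding.
- **Weekly days of use:** adjust the comparison for the baseline value.
- **Presentation:** show median and IQR for both.
- **Consistency:** either drop the generalized estimation equations from the abstract or describe them in section 2.7 with link and distribution.

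This costs analysis wording only; no extra data or participants are needed. The downside is real. The morphine effect becomes a ratio or a rank-based measure, not a difference in mean level. Power can also be lower than on the raw scale if treatment changes only users' levels and leaves the share at the floor unchanged.

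### The Abstract and section 2.7 name different between-group analyses, and the t test in 2.7 is not adjusted for the baseline value collected for every outcome

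*Protocol article*

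**What the plan says.** Three places in the protocol article bear on how the arms are compared.

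- Abstract, Methods: "Data between the 2 groups will be compared using generalized estimation equations". Paired t tests are listed alongside.
- Section 2.7: "The differences between the 2 groups will be compared using an independent *t* test". The next sentence gives a paired t test the task of comparing the two groups. GEE is not mentioned, no covariate is named, and it is not stated whether the independent t test is applied to week-4 values or to change from baseline.
- Section 2.4: "We calculated a sample size of 98 in accordance with a 2-way repeated-measures analysis of variance with a medium effect size of 0.25", with "pre- and post-measurements for each of the 2 groups" and "a significance level (*α*) of 0.05, and a desired power (1–*β*) of 0.80". Then: "Expecting a 2% dropout rate, 100 participants will be recruited". No pre-post correlation is given.

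Section 2.6 has both primary outcomes (urinary morphine and self-reported heroin use in the past week), the secondary outcomes, pulse diagnosis and heart rate variability all recorded before and after the 4 weeks.

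**The concern.** A reader cannot tell which between-group test will decide the trial. The Abstract and 2.7 give different answers, and part of 2.7 cannot be carried out as written: a paired t test needs matched pairs, and the two arms are independent.

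Two things are at stake. First, precision: the baseline value is already collected, and in a randomised comparison adjusting for it can only help to the extent that it predicts the week-4 value. An independent t test does not adjust for it. Second, error control: when two tests of the same effect are both consistent with the text, each primary outcome has more than one defensible P value. The nominal 5% holds only if the choice is made without sight of the results.

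**Working it through.** **Inputs from section 2.4.** Effect size f = 0.25; 2 groups; 2 measurements; alpha 0.05; power 0.80; N = 98, raised to 100 for 2% dropout.

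**Assumptions, not in the document.** Pre-post correlation rho (0.3, 0.5 and 0.7 shown); two-sided tests; normal outcomes with equal SD before and after; a true week-4 difference of d = 0.5 SD (for two groups d = 2f = 0.5, but placing that difference at week 4 is a choice made here).

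**Step 1: the plan's own figure.** For the between-groups effect in a repeated-measures ANOVA with m = 2 measurements, the noncentrality is lambda = N·m·f² / (1 + (m − 1)·rho), on 1 and N − 2 degrees of freedom. With N = 98 and rho = 0.5, lambda = 98 × 2 × 0.0625 / 1.5 = 8.17 and power is 0.808. The smallest even N reaching 0.80 is 98, and 98 / 0.98 = 100. The stated figures reproduce. At rho 0.3 and 0.7 the same formula needs 84 and 110. The group-by-time interaction with the same f and rho = 0.5 needs only 34. So 98 matches a group difference averaged over the pre and post measurements.

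**Step 2: power of the candidate analyses at 49 per arm.** The noncentrality of the t test is (d / s)·√(49/2), where s is the SD multiplier:

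- week-4 values: s = 1
- change: s = √(2(1 − rho))
- ANCOVA, week-4 value adjusted for baseline: s = √(1 − rho²)

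Worked at rho = 0.5: week-4 values and change both give 0.5 × 4.950 = 2.475, power 0.69. ANCOVA gives (0.5 / 0.866) × 4.950 = 2.858, power 0.81.

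| rho | t test, week 4 | t test, change | ANCOVA |
|---|---|---|---|
| 0.3 | 0.69 | 0.54 | 0.73 |
| 0.5 | 0.69 | 0.69 | 0.81 |
| 0.7 | 0.69 | 0.89 | 0.93 |

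For 0.80 power at rho = 0.5, either t test needs N = 128 and ANCOVA needs 98. ANCOVA has the most power in every row, so precision is lost whichever way 2.7 is read. The gain over the better t test is 4 points at rho 0.3, 12 at 0.5 and 4 at 0.7.

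**Step 3: error rate if the test is chosen after seeing the data.** In null simulations with 49 per arm and rho of 0.3, 0.5 and 0.7, each t test alone rejects in about 5% of trials. Rejecting when either the week-4 or the change t test is significant gives about 9% (0.087 to 0.094 across runs).

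**The case against.** Several stronger readings are tempting, and the document does not support them.

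*Three rival efficacy analyses.* A reader might count the repeated-measures ANOVA as a third. Section 2.4 uses it only to size the trial. The direct conflict is between GEE and the independent t test. Nor do these necessarily target different effects: under randomisation, the two t tests, ANCOVA and a GEE group-by-time term all address the same week-4 mean difference.

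*Section 2.7 ignores baseline.* Not established. A t test on change uses the baseline without adjusting for it, and 2.7 does not rule that out.

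*The trial has only 69% power.* This does not follow. The 98 matches an effect averaged over pre and post. With equal baselines, an average difference of 0.5 SD means about 1.0 SD at week 4, where both t tests have at least 98% power for rho from 0.3 to 0.7. ANCOVA's 81% meets the planned 80% only because the two formulas coincide at rho = 0.5. On change at rho = 0.7, the t test exceeds the target.

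*Type I error is inflated.* Only if the choice follows the results, and nothing says it will. A higher figure could be produced by adding a test of the group main effect, but the protocol never proposes that as an efficacy analysis.

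It is also fair to say that an unadjusted t test is valid in a randomised trial, and that an analysis plan not shown here may settle covariates and the choice between week-4 values and change. That answers a complaint about missing detail. It does not remove the contradiction, because such a plan could agree with the Abstract or with 2.7 but not with both as they stand. The normality caveat also stands: urinary morphine is a concentration and times or days of use in a week is a count, so the power figures are approximate and a plain linear ANCOVA may not suit either outcome.

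**Conclusion.** The concern holds in this form. The article gives two different between-group analyses, describes a paired test as a comparison of independent arms, and leaves the baseline out of the test in 2.7 as a covariate. The contradiction is in the text, rests on no assumption, and should be settled before unblinding. Blinding the analysts with A and B labels, as in 2.4, does not settle it, because P values can be compared under coded labels.

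The size of the precision loss does rest on assumptions: normal data, d = 0.5 at week 4, 98 analysed and an unstated correlation. Under these, ANCOVA gains between 4 and 12 points of power over the better of the two t tests for rho from 0.3 to 0.7, and up to 24 points over a t test on week-4 values (0.93 against 0.69 at rho = 0.7). The error rate of about 9% applies only to a choice between the two t tests made after seeing the data.

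**What to change.** - Name one primary between-group analysis, in the same words, in the Abstract and in 2.7: the week-4 value on treatment group, adjusted for the baseline value, reported as a treatment difference with 95% CI.
- Provide for skewed outcomes in advance: a transformed scale, or a count or robust-variance model such as GEE with baseline adjustment, for urinary morphine and for times or days of use.
- Limit paired t tests to descriptive change within each arm.
- In 2.4, state the effect (which contrast, at which time) and the pre-post correlation assumed, so that the sample size refers to the analysis named in 2.7.

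The cost is wording and slightly more analysis work. The baseline values are already being collected, so no new data are needed.

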### 2.2. Study design

This randomized controlled trial is being conducted in the Department of Psychiatry and Chinese Medicine at Kaohsiung Chang Gung Memorial Hospital. The study was initiated in March 2022 and will continue until February 2024. Patients enrolled from our institution’s addiction treatment center are being randomly allocated to the experimental group (light needle plus methadone maintenance treatment, n = 50, expected) or the control group (light needle without laser output plus methadone maintenance treatment, n = 50, expected). The study participants will receive 12 sessions of light needle therapy within 4 weeks. The study design is illustrated in Figure 1.

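### The paired t test is given the job of comparing two independent randomised arms, which it cannot do; a valid between-arm test is also named, but the plan does not say which one decides efficacy.

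*Protocol article*

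**What the plan says.** The statistical analysis section (2.7) gives two tests for comparing the arms, in consecutive sentences. The first is "The differences between the 2 groups will be compared using an independent *t* test". The second is "Paired *t* test will be used to compare the 2 groups".

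The Methods paragraph of the Abstract gives a different pair: "Data between the 2 groups will be compared using generalized estimation equations, and paired *t* tests".

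The design is parallel and individually randomised. Section 2.2 says "Patients enrolled from our institution’s addiction treatment center are being randomly allocated to the experimental group" or to the control group, 50 expected in each. Section 2.4 describes the allocation: "A random permutation block of block size 4 is selected using a research randomizer that generated a random sequence". No matching of patients across arms and no crossover is described. Section 2.6 has the primary outcomes measured "during the previous week before and after the 4-week intervention period", and the other outcomes are likewise taken before and after.

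Neither section 2.7 nor the Abstract limits the paired t test to change within an arm, and neither says which test carries the efficacy conclusion.

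**The concern.** A paired t test needs a real link between the two members of each pair. No patient in the laser arm is linked to a patient in the sham arm, so the test cannot serve the purpose that both places give it.

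The one link the data do contain is each participant's before and after values. A paired test on those asks whether an arm changed over four weeks. It does not ask whether laser changed patients more than sham did. Both arms stay on methadone and both attend 12 sessions, so change common to both arms is possible, and a within-arm test cannot separate it from a laser effect.

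Because the paired test is labelled a group comparison and stands beside valid ones with no order of priority, the plan leaves open which result supports a claim. What is at stake is the basis of the efficacy conclusion for every outcome tested this way, including both primary outcomes.

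**Working it through.** **1. Is the paired test behind the planned sample size?** No. Section 2.4 says "We calculated a sample size of 98 in accordance with a 2-way repeated-measures analysis of variance with a medium effect size of 0.25", with "pre- and post-measurements for each of the 2 groups", α = 0.05 and power 0.80. The article gives no correlation between the two measurements; I assume 0.5. For the between-group factor of that model, the noncentrality is λ = f² × N × m / (1 + (m − 1)ρ) = 0.0625 × 98 × 2 / 1.5 = 8.17. With 1 and 96 degrees of freedom the power is 0.808, and 98 is the smallest even total that reaches 0.80. Then 98 / 0.98 = 100. The stated figures therefore reproduce under a repeated-measures model with a between-group factor. The sample size is not affected by this point.

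**2. The paired test taken literally, across arms.** With equal numbers of completers, software would run it, pairing patients by row order. With unequal numbers, some patients have no partner. As an illustration, one data set was simulated with 50 per arm and a true difference of 0.5 SD, and the patients were re-paired at random 5,000 times. The paired P value ranged from 0.002 to 0.053. The independent t test on the same data gave a single value, 0.015. The paired result depends on an ordering that carries no information.

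**3. The paired test read as before-after within each arm.** This is a legitimate test of change, but not of treatment. To see the cost of using it as a treatment comparison, one further assumption is needed that the plan does not make: that efficacy is claimed when the laser arm is significant and the sham arm is not.

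Inputs:
- n = 50 per arm (section 2.2).
- Two-sided α = 0.05 (section 2.7 gives P < .05; two-sidedness is assumed).
- The same true standardised change dz in both arms, that is, no treatment effect. The article gives no expected change, so dz is an assumed range.
- Independent arms.

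Formulas:
- Power per arm, p: noncentral t with 49 degrees of freedom, noncentrality dz × √50, critical value 2.01.
- Exactly one arm significant: 2p(1 − p).
- Only the laser arm significant, in the favourable direction: p₊ × (1 − p), where p₊ is the part of the power in that direction. At dz = 0 this is 0.025 × 0.95. From dz = 0.2 upward p₊ is practically p.

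| dz in both arms | power per arm | exactly one arm significant | laser only, favourable |
|---|---|---|---|
| 0 | 5% | 9.5% | 2.4% |
| 0.2 | 28% | 41% | 20% |
| 0.28 | 49% | 50% | 25% |
| 0.4 | 79% | 33% | 16.5% |
| 0.5 | 93% | 12% | 6% |

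Worked line at dz = 0.4: p = 0.792; 2 × 0.792 × 0.208 = 0.33; 0.792 × 0.208 = 0.165.

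A proper two-sided 5% test of laser against sham would wrongly favour laser 2.5% of the time, whatever the shared change. The within-arm rule matches that at dz = 0, is worst near dz = 0.28, where each arm has about 50% power, and falls again as both arms become significant together.

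**The case against.** The strongest reply is that the plan already contains a valid comparison. The sentence just before the faulty one in section 2.7 assigns the independent t test to the group differences, and the Abstract names GEE. With that in place, the authors most likely meant the paired test for before-after change, and this is a slip of wording in a condensed article. Most of this stands. The trial does not lack a treatment comparison, and the independent t test is not damaged by the sentence that follows it. What does not stand is the idea of an isolated slip: the Abstract gives the paired test the same role, and neither place mentions change within an arm.

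A reader might infer that efficacy will be claimed if the laser arm is significant and the sham arm is not. The documents do not support that; no such rule is stated, and testing change within arms does not entail it. The percentages above describe a misuse the wording leaves room for, not a property of the stated plan. They also depend on an equal change in both arms, for which the article gives no figure, and the range of 0.2 to 0.4 surrounds the worst case.

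A reader might also infer that the paired test is impossible to run. That is too strong: with equal numbers of completers it runs, but the answer has no meaning.

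**Conclusion.** The point holds as an error in the stated role of the paired t test. In both places it is named as a comparison of two independent arms, for which no valid pairing exists; its only sound use here is to describe change within an arm. The plan does include a valid between-arm method, but it names different ones in the two places, puts the paired test beside them, and does not say which decides efficacy.

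The size is conditional. Under the unstated one-arm-only rule, with equal change in both arms, independent arms and 50 per arm, the false laser-only finding runs from about 2.4% to a peak of 25%, against 2.5%. If efficacy is concluded only from the independent t test or from GEE, this inflation does not arise. Sample size and randomisation are untouched. The correction should be made before the data are analysed, because it settles what counts as evidence of effect.

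**What to change.** In section 2.7 and in the Abstract, relabel the paired t test as a description of before-after change within each arm, and remove it from the methods for comparing groups. In both places, state that efficacy is concluded solely from one named between-arm analysis, the same in each: either the group-by-time term from GEE or the independent t test on change. Report it as a difference between arms with its 95% confidence interval. Whether P values are shown for within-arm change is optional once the label is right.

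The cost is a few sentences in two places. No data, visits or patients are added.
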